#### Education and collaboration

Healthcare professionals will receive education during the 3-month wash-out period: GPs 2 × 3 h and therapists 3 × 3 h. Topics in the education program include biopsychosocial theories of CMP, recognition of patients with or at risk of CMP, providing education to patients with CMP, use of the assessment tool and eHealth application, and treatment selection. The first two sessions are organized jointly for all disciplines of healthcare professional in order to promote a common understanding of biopsychosocial treatment. Separately, therapists will also receive information about the treatment protocols. To encourage collaboration in the local networks, three additional peer-review meetings of one hour (every 6–8 weeks) are organized by the project team in each local network after the wash-out period. During these meetings, healthcare professionals apply the theories and treatment protocols learned during the education program in daily practice, with room for extra education by the teachers if necessary. After these three peer-review meetings, the local networks are encouraged to organize further such meetings in order to align the working procedures and treatment plans of the patients.

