**Fig. 3 Fig3:**
[figure not shown]
Content of data collection in ‘Patients in cohort’: patients participating in the prospective cohort design; ‘Patients in stepped-wedge based control period: data collection for patients participating in the control group of the stepped-wedge based design; ‘Patients in stepped-wedge NPRL2.0; data collection for patients participating in the intervention group of the stepped-wedge design

Patients participating in NPRL2.0 are asked to fill in four questionnaires electronically or on paper: T1 after initial contact with healthcare professionals about their CMP complaints (50 min completion time); T2 3 months after T1 (30 min completion time); T3 6 months after T1 (30 min completion time); and T4 9 months after T1 (50 min completion time).

Additionally, assessment tool 1 will be used for research purposes, as well as for decision-making in primary care. Therefore, patients in the control group will complete assessment tool 1 as part of the questionnaire at T1. Patients in the intervention group will complete it during their consultations in primary care. Assessment tool 1 will assess the level of complexity of the pain complaints and consists of one Visual Analogue Scale (VAS) for pain intensity and nine dichotomous questions on biopsychosocial factors.

At the end of the study, records of the treatment characteristics of each patient will be collected from the participating practices and rehabilitation centers.

In order to encourage completion of the questionnaires, patients will be reminded up to three times by phone if they have not responded within one week. If incomplete questionnaires are returned, patients will be contacted by phone to answer the remaining questions. The researcher who performs the analyses will be blinded as to patient allocation.

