### Data analysis

Demographic data (e.g. gender, age, home situation, level of education, nationality, and co-morbidities) will be described overall and separately for the intervention and control groups. Frequencies are to be presented for categorical variables, means and standard deviations (SDs) for normally-distributed continuous variables, and medians and ranges for non-normally-distributed continuous data. The two groups will be tested on differences between characteristics, using the *t*-test for continuous variables and the chi-squared test for categorical variables. If variables differ between the two groups, with *p* ≤ 0.10, they are considered to be potential confounders in further analyses.

Outcomes on questionnaires will be compared using linear mixed-model analysis, to take into account repeated measurements in patients as well as the effects of the clustering of patients within local networks. The fixed part of the model contains treatment group (intervention/control), time, treatment group*time, and cluster (local network). To assess the learning effect in local practices, the time (months) that a local network participates in NPRL2.0 will also be taken into account as a fixed variable. Variables known to be related to the outcome and differing between treatment groups at T1 (*p* ≤ 0.10) will be added to the model. An unstructured covariance structure will be used for repeated measures. Missing values for items in the questionnaires will be handled according to the scoring algorithms of the questionnaires. Missing variables in the follow-up data will not be imputed because linear mixed-model analysis is a flexible method for handling missing data for stepped-wedge and repeated-measures designs (likelihood-based approach). Linear mixed-model analyses will be performed using IBM SPSS Statistics for Windows (version 24.0 or higher, Armonk, NY: IBM Corp.) according to the intention-to-treat principle. Other missing values for non-repeated measures will be handled by multiple imputation, which means that missing values will be predicted using existing values for other variables [66].

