## Discussion

The Network Pain Rehabilitation Limburg 2.0 (NPRL2.0) has been developed in order to provide integrated care with a biopsychosocial approach for people with CMP with the goal of improving their level of functioning. Moreover, it is intended to accomplish the Quadruple Aim: improvement of pain-related disability of people with CMP; improvement of experiences of care of people with CMP; improvement in the meaning of work for healthcare professionals; and the reduction of healthcare costs of people with CMP. In this quantitative study, the effectiveness of NPRL2.0 in reducing the pain-related disability of people with CMP will be assessed. In addition, the influence of NPRL2.0 on healthcare costs will be examined with a cost-effectiveness and cost-utility analysis. Moreover, the learning curve of healthcare professionals working in NPRL2.0 will also be studied.

NPRL2.0 is a multidimensional, complex intervention, executed in daily practice [33]. Because of the practice-based approach of this study, a randomized controlled trial design (RCT) is not suitable. Therefore, a pragmatic study with stepped-wedge based design using randomization of the local networks was seen as a viable alternative to an RCT [70]. The local primary care networks involved would be randomly assigned to the three steps (A, B or C) in order to randomize the duration of being a control group or intervention group. Local networks are their own controls in a stepped-wedge based design. Healthcare professionals are instructed to recruit patients at their first consultation for CMP complaints. Therefore, it is expected that patients with comparable complexities of complaints will be distributed equally over the control and intervention groups. Moreover, in this practice-based research, connections between science, policy, and practice exist during implementation and execution of NPRL2.0, leading to evidence-based practice. The external validity of the results of such as this pragmatic study of NPRL2.0 is commonly higher than that of RCTs because the results are more generalizable.

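### Baseline covariates are selected by a p ≤ 0.10 test between patient groups that were not randomised, so prognostic imbalance can go unadjusted

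*Protocol article*

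**What the plan says.** The Data analysis section of the protocol article sets the rule in two steps. First, "The two groups will be tested on differences between characteristics", "using the *t*-test for continuous variables and the chi-squared test for categorical variables". Variables with p ≤ 0.10 pass the screen: "they are considered to be potential confounders in further analyses". Second, the mixed model takes in "Variables known to be related to the outcome and differing between treatment groups at T1", again at p ≤ 0.10. The terms that are always present are treatment group, time, their interaction, local network, and months of participation in NPRL2.0. None of these is a patient characteristic.

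Under Study design, networks are randomised to step A, B or C. Each network recruits controls, then has a 3-month wash-out with education, then recruits other patients under NPRL2.0. The topics taught include "recognition of patients with or at risk of CMP". The Discussion argues for balance by expectation: "it is expected that patients with comparable complexities of complaints will be distributed equally over the control and intervention groups". Under Data collection, controls complete assessment tool 1, the complexity measure, in the T1 questionnaire. For the others, "Patients in the intervention group will complete it during their consultations in primary care".

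**The concern.** Randomising the steps fixes when a network changes over, not which patients fall in which group. The same professionals recruit both groups and are trained in between. Eligibility also leaves room for judgement (high risk of chronicity, willingness to improve functioning, exclusion on the GP's opinion). Covariate adjustment is therefore the main protection against case-mix differences within a network.

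A significance screen is poor protection. Whether a covariate enters depends on sample size and chance rather than on how strongly it predicts outcome. The tests also pool over networks, whereas the model compares within network. With 3:5 control-to-intervention months in Group A and 5:3 in Group C, network mix can hide or create a pooled difference. At stake are residual confounding of a before-after contrast and an adjustment set that is not known until the data are in.

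**Working it through.** **Inputs.** 184 patients, 92 per group, target 0.063, printed SD 0.013, design effect 0.416, dropout 30%, 6 patients per network per month (Sample size); screen at p ≤ 0.10, taken as two-sided (Data analysis); period lengths (Study design). Covariate-outcome correlations of 0.3 to 0.5 are my assumption.

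**1. The plan's own figure.** For two means, two-sided 5%, 80% power, total N = 4 × (1.960 + 0.842)² × (SD/0.063)² = 31.40 × (SD/0.063)². With SD 0.013 this is 1.3, or one patient per arm, so the printed SD cannot yield 184. Working back from 184 × 0.7 = 128.8:
- without the design effect, SD = 0.063 × √(128.8/31.40) = 0.128;
- with it, 128.8/0.416 = 309.6 and SD = 0.063 × √(309.6/31.40) = 0.198.

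I use 0.128 to 0.198 only as an assumed range for the utility SD. The screening results below need only the group size.

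**2. Calendar.** Each group spans 11 months (3+3+5, 4+3+4, 5+3+3). Assuming a common start, control recruitment ends in month 3, 4 or 5 and intervention recruitment starts in month 7, 8 or 9. The latest control month (5) precedes the earliest intervention month (7), so there is no concurrent randomised contrast between patients.

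**3. Largest observed difference that escapes the screen**, 1.645 × √(2/n):
- n = 92: 0.243 SD;
- n = 64 (92 × 0.7): 0.291 SD;
- n = 144 (6 × 2 × (3+4+5), the expected recruitment): 0.194 SD.

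For a binary factor at n = 92 this is 0.243 × √(0.5 × 0.5) = 12 percentage points near 50%, or 0.243 × √(0.25 × 0.75) = 10.5 points near 25%.

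**4. Probability that a covariate with true difference d is left out**, Φ(1.645 − d/s) − Φ(−1.645 − d/s), with s = √(2/n):

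| d (SD) | n = 64 | n = 92 | n = 144 |
|---|---|---|---|
| 0.1 | 0.85 | 0.82 | 0.78 |
| 0.2 | 0.69 | 0.61 | 0.48 |
| 0.3 | 0.48 | 0.35 | 0.18 |
| 0.4 | 0.27 | 0.14 | 0.04 |

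**5. Upper case for a comparison of follow-up levels.** A difference just under the threshold shifts the contrast by 0.243 × 0.3 = 0.07 SD to 0.243 × 0.5 = 0.12 SD per covariate. In utility this is 0.073 × 0.128 = 0.009 (15% of 0.063) to 0.1215 × 0.198 = 0.024 (38%).

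**6. Group-by-time contrast.** With T1 as an outcome point and equal SDs, the shift is 0.243 × (r at T4 − r at T1). Correlations of 0.5 at both times give zero. Correlations of 0.5 at one time and 0.4 at the other give 0.243 × 0.1 = 0.024 SD, or 0.003 to 0.005 in utility, 5% to 8% of 0.063.

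**7. Average over the screening.** A simulation of follow-up levels used 92 per group, no treatment effect, d of 0.1 to 0.3, correlations of 0.3 or 0.5, and 2,000 trials per scenario. Mean bias under the screen was 0.01 to 0.03 SD for one confounder and 0.05 to 0.10 SD for three in the same direction. Type I error was close to 0.05 except in the worst scenarios (three confounders, correlation 0.5, d of 0.2 or 0.3), where it was about 0.08, against about 0.05 with all covariates always included. Bias with all included stayed within ±0.006 SD.

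**8. QALYs.** With utilities at 0, 3, 6 and 9 months and trapezoids, T1 carries weight 0.125 year out of 0.75. A T1 utility difference u therefore adds 0.125u to the QALY difference if it vanishes by T2, and 0.75u if it persists.

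**The case against.** The best defence is the model itself. Network is a fixed effect and every network supplies both groups, so stable differences between networks are controlled. T1 is an outcome point, so a stable baseline difference in the outcome is removed by the interaction. One set of eligibility criteria applies throughout, and recruitment is meant to occur at the first consultation. All of this stands, and it limits the point to covariates that predict change and to analyses that do not condition on T1.

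Some stronger readings are tempting but are not supported:

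- *That the trial's effect is biased by 38% of its target.* That figure needs an imbalance exactly at the threshold, a correlation of 0.5, the larger back-calculated SD, and a comparison of levels rather than change. It is an upper case, not an expectation.
- *That a case-mix shift is certain.* Training makes one plausible; the document gives no evidence that it occurs.
- *That comparability cannot be checked.* PDI, SF-12, EQ-5D-5L and pain NRS are all collected at T1 in both groups.
- *That assessment tool 1 is not comparable between groups.* It is one instrument used in two settings. A mode effect is possible but not shown.
- *That nothing was randomised.* Networks were, to steps; patients were not.

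**Conclusion.** The point holds in a limited form. The rule can leave prognostic imbalance unadjusted in a comparison where patients are not randomised: nothing below 0.243 SD is adjusted at 92 per group, and a true 0.2 SD difference is missed about six times in ten. In the mixed model the bias is likely small for one covariate and larger for several that predict change in the same direction. For comparisons of levels the upper case is 15% to 38% of 0.063 per covariate, resting on the assumed correlations and utility SDs above.

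The QALY and cost comparisons are more exposed. They are described as bootstrapped mean differences with no baseline adjustment stated. If the general reference to further analyses is meant to cover them, they inherit the same screen. The trial remains analysable. This is a nearly free improvement, not a fatal flaw.

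**What to change.** 1. Remove the p ≤ 0.10 rule. Name a prognostic set in advance and include it whatever the baseline difference: age, gender, education, co-morbidities and pain NRS, all already collected at T1. Keep the T1 outcome value in the model. If T1 stays as an outcome time point, enter each covariate with its interaction with time: with complete data, a main effect alone leaves the group-by-time contrast unchanged.
2. Report the baseline table descriptively, without using tests to select covariates.
3. Adjust the QALY difference for T1 utility and the same covariates.
4. Optionally, put assessment tool 1 in the T1 questionnaire for both groups, so that complexity is measured in the same way and can join the set.

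Items 1 and 2 cost a change of wording and a few degrees of freedom. Item 3 is a small added analysis, since the plan describes no economic regression. Item 4 asks intervention patients to answer ten short items twice.

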**Methods:**

In this pragmatic study, it is expected that two local networks with 105 patients will participate in the prospective cohort study and six local networks with 184 patients in the stepped-wedge based design. Healthcare professionals in the local networks will recruit patients. Inclusion criteria: age ≥ 18 years; having CMP; willing to improve functioning despite pain; and adequate Dutch literacy. Exclusion criteria: pregnancy; and having a treatable medical or psychiatric disease. Patients will complete questionnaires at baseline (T1), 3 months (T2), 6 months (T3), and 9 months (T4). Questionnaires at T1 and T4 will include the Pain Disability Index and Short Form Health Survey. Questionnaires at T1, T2, T3, and T4 will include the EQ-5D-5L, and iMTA Medical Consumption and Productivity Cost Questionnaires. Outcomes will be compared using linear mixed-model analysis and costs will be compared using bootstrapping methods.

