### Sample size

In the prospective cohort, all patients with CMP who visit the two local networks of NPRL1.0 will be invited to participate in the study. Based on the recruitment results of the feasibility study of NPRL1.0, and the number of patients visiting a GP practice, we expect that each local network will also recruit about six patients per month. Therefore, the two local networks from NPRL1.0 together should recruit approximately 132 patients in 11 months. Assuming a dropout rate of 20%, we expect to include approximately 105 patients in this study.

To calculate the desired sample size for the stepped-wedge based design, we used the method described by Woertman et al. [39]. The calculations of the number of patients needed are based on the primary outcome of the cost-utility analysis, the health-related quality of life measured with the 5-level EQ-5D version (EQ-5D-5L). Based on McClure et al., we consider an increase of 0.063 points (SD = 0.013) in 1 year as clinically relevant [40]. In addition, an alpha of 0.05, a power of 80%, a 1:1 ratio between control and intervention groups, and a dropout rate of 30% were assumed. Based on these values and the stepped-wedge based design, a design effect (DEsw) of 0.416 exists, which leads to a required sample size of 184 patients (92 control and 92 intervention). Based on the recruitment results of the feasibility study of NPRL1.0, and the number of patients visiting a GP practice, we expect that each local network will recruit 6 patients per month [32]. Therefore, with a dropout rate of 30% of local networks, six local networks will need to participate.

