#### Health assessment

The Pain Disability Index (PDI) will be used as the primary outcome for pain-related disability. It measures the influence of pain on a patient’s life and on the performance of daily activities. The questionnaire consists of seven items that measure the complexity of the disabilities experienced in different situations such as work, leisure time, activities in daily life, and sport. Each item is scored on a scale from 0 (no disability) to 10 (severe disability). Scores from the individual items are summed to a total (0–70). The minimal important change is 13 points for patients with CMP [41]. The Dutch version of the PDI has proven internal consistency and test–retest reliability [42].

The Dutch language version of the Short Form Health Survey (SF-12) will be used as the primary outcome for cost-effectiveness, measuring quality of life on specific domains. The SF-12 has proven to be a practical, reliable, and valid instrument for use in both general population surveys and in studies of chronic disease populations in the Netherlands [43, 44]. The SF-12 will be summarized into two scales: a physical component score (PCS) and a mental component score (MCS), in accordance with the guidelines for the SF12 instrument [45]. The PCS comprises the domains of physical functioning, physical role limitation, bodily pain, and general health perceptions. The MCS comprises the domains of vitality, social functioning, emotional role limitations, and general mental health. Both scores range from 0 to 100 (a higher score indicates a better quality of life) with a minimal clinically important difference of 8.9 for low back pain [46]. These sub-scales will be used in the effectiveness analysis. Besides the SF-12 score, the Short-Form Health Survey with six dimensions (SF-6D) scores will be used in a sensitivity analysis.

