The EQ-5D-5L will be used for the cost-utility analysis: it provides a single health index based on self-reported mobility, self-care, usual activities, pain/discomfort, and anxiety/depression, with a minimal clinically important change of 0.04 [47]. There are five levels in each dimension from which respondents select that which most closely matches their health state. The levels are no, slight, moderate, severe, and extreme problems, coded 1 to 5. A health state index score, ranging from − 0.446 to 1 (worst to best imaginable health status), will be calculated from individual health profiles, using the Dutch utility tariff [48]. QALYs were calculated from utilities by using the area under the curve method. The accompanying visual analogue scale (VAS: 0–100) rates the current health state, with higher scores indicative of better experienced health. The minimal clinically important difference for low back pain is 22.5 [46]. The Dutch version of the EQ-5D-5L was found valid and reliable [49, 50].

The Numeric Rating Scale (NRS) will be used to measure pain intensity on an 11-point scale varying from 0 (no pain) to 10 (worst pain imaginable). At each measurement point (T1-4), the patient will complete the NRS three times: current pain intensity; lowest pain intensity in the last week; highest pain intensity in the last week. The NRS has shown high test–retest reliability and validity [51]. A reduction of 2 points, or 30%, on the pain NRS scores can be seen as clinically important [52].

The Hospital Anxiety and Depression Scale (HADS) consists of 14 items of which seven are related to anxiety and seven to depression. The patient is asked to rate the items on a 4-point scale ranging from 0 (not at all) to 3 (most of the time). Total scores range from 0 to 21 on each subscale: a higher score reflects higher distress. The HADS has a sensitivity and specificity of about 80% and a predictive validity for identification of about 70% [53]. The reliability ranges from 0.84 to 0.96 [54].

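### PDI and SF-12 have a single follow-up value, so the mixed model is a weak reason not to impute them, and not using the 3- and 6-month pain and EQ-5D-5L data can bias the PDI contrast

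*Protocol article*

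**What the plan says.** On the outcome, the Health assessment section says "The Pain Disability Index (PDI) will be used as the primary outcome for pain-related disability". On timing, the abstract says "Questionnaires at T1 and T4 will include the Pain Disability Index and Short Form Health Survey", whereas "Questionnaires at T1, T2, T3, and T4 will include the EQ-5D-5L, and iMTA Medical Consumption and Productivity Cost Questionnaires". Pain intensity is also collected on all four occasions: "At each measurement point (T1-4), the patient will complete the NRS three times".

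On the model, the Data analysis section says "The fixed part of the model contains treatment group (intervention/control), time, treatment group*time, and cluster (local network"). It adds months of network participation and covariates that are related to the outcome and imbalanced at T1. No T2 or T3 variable enters. On missing follow-up values it says "Missing variables in the follow-up data will not be imputed because linear mixed-model analysis is a flexible method for handling missing data". Multiple imputation is kept for measures that are not repeated, and all four sensitivity analyses concern the economic evaluation.

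On attrition, the Sample size section says, for the stepped-wedge part, that "a dropout rate of 30% were assumed". For the prospective cohort it assumes 20%.

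**The concern.** A likelihood-based mixed model deals well with dropout when patients leave some of their own post-baseline outcome values behind, because the later missing values are then predicted from the earlier ones. PDI and SF-12 leave none. With two occasions, a patient without T4 contributes only T1, and the model in effect predicts T4 from T1 using the completers of the same group. If patients leave because of how they are doing at 3 or 6 months, the model cannot see it, although their NRS and EQ-5D-5L at those visits may be in the database.

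What matters is the difference between groups. Only intervention patients have the app with diaries and chat, patients and clinicians know which care is given, and control patients are recruited before intervention patients in each network. Equal dropout mechanisms are therefore not secured by the design. If intervention patients who recover early stop responding, the intervention T4 mean is too high (worse). If control patients who do not improve stop responding, the control mean is too low (better). Both count against the intervention, and the reverse patterns would favour it. The direction cannot be told in advance.

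**Working it through.** The article gives no figure for this bias, so there is none to reproduce. The 184 patients are taken as given; how that number was reached (from EQ-5D-5L) is a separate question.

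**1. Patients affected.** Inputs from the Sample size section: 184 patients, 30% dropout. If 184 is the number enrolled, 184 × 0.30 = 55 have no T4 PDI and 184 × 0.70 = 129 have one, about 64 per group.

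**2. Precision.** Assumed: PDI SD 14, T1–T4 correlation 0.5; clustering ignored. SE = 14 × √(1 − 0.5²) × √(2/64) = 12.1 × 0.177 = 2.1 points; with SD 13 it is 2.0. The 95% half-width is about 1.96 × 2.1 = 4.2.

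**3. Bias in one group.** Let A be the interim status that drives dropout, with log-odds β per SD, and let d be the dropout proportion. Completers differ from all patients in mean A by δ = β × E[p(1 − p)]/(1 − d), where p is the individual dropout probability. A model that conditions on T1 only is then off by about

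SD × (r(A,T4) − r(T1,T4) × r(T1,A)) × δ.

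Assumed: SD 13, r(T1,T4) = 0.5, r(T1,A) = 0.35, d = 0.30.
- β = 1: E[p(1 − p)] = 0.177, so δ = 0.177/0.7 = 0.253. With r(A,T4) = 0.6: 13 × (0.6 − 0.175) × 0.253 = 1.4. With r(A,T4) = 0.4: 13 × 0.225 × 0.253 = 0.74.
- β = 0.5: E[p(1 − p)] = 0.200, so δ is about 0.14, giving 0.78 and 0.41.

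Large simulations (1,000,000 patients per group) agree: 1.40, 0.74, 0.78 and 0.41.

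**4. Bias in the contrast.** This is the difference between the two group biases, at about 30% dropout unless stated.

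| Dropout pattern | Bias (PDI points) |
|---|---|
| Same relation and rate in both groups, no effect | 0.0 |
| Same relation, unequal rates (35–40% v 20–25%), SD 14 | 0.2–0.8 |
| Related to status in one group only | 0.4–1.4 |
| Opposite relations in the two groups | 1.4–2.8 |
| Same relation, true effect of 6.5 points that also shifts early status | 0.1–0.8, toward no effect |
| The same with a 13-point effect | 0.3–1.6, toward no effect |

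In the last two rows dropout rises above 30% in the intervention group, to as much as 61% in the extreme case. At 20% dropout, the one-group and opposite patterns give 0.3–1.0 and 1.0–2.0.

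**5. Consequence for the test.** With no true effect, a bias of 1.4 points is 1.4/2.1 = 0.67 SE. Two-sided rejection is then Φ(−1.96 + 0.67) + Φ(−1.96 − 0.67), about 10% instead of 5%. At 2.7 points (1.29 SE) it is about 25%.

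**6. What the interim data recover.** If the auxiliary is itself the dropout driver and every dropout has a value for it, the bias falls to about 0. That case is favourable by construction. With SD 14, r(A,T4) = 0.65 and an odds ratio of 1.75, the plan's bias is about 0.6 (unequal rates), 1.1 (one group) and 2.1 (opposite). With an auxiliary that correlates 0.7 with the driver and is missing in half of the dropouts, it falls only to about 0.4, 0.8 and 1.6.

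**The case against.** A mixed model without imputation is a recognised missing-at-random analysis, also with two occasions, and an article may leave auxiliary variables, missing-data sensitivity analyses and dropout tables to an analysis plan. Follow-up rests on research questionnaires with up to three telephone reminders, described without distinction between groups, so stopping treatment is not the same as leaving the study. That the app changes questionnaire return is an inference. The bias is below one standard error in most scenarios and at most 2.8/13 = 22% of the minimal important change.

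Most of this stands, and it limits the point. A reader might infer that the primary contrast is biased; the documents show no difference in dropout between groups, and with the same mechanism and no effect the bias is zero. A reader might also infer that the interim data would remove the bias, or that the planned model must be replaced. Step 6 contradicts the first. The second does not follow, because the planned model is valid under its own assumption.

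Two things are not answered. The article does not leave the matter open: it fixes a no-imputation rule and gives a reason that fits PDI and SF-12 poorly. And 13 points is a threshold for change, while the Discussion expects no short-term benefit and outcomes no worse than usual care. For a contrast expected near zero, the standard error is the closer yardstick.

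**Conclusion.** The point holds as a conditional weakness. For PDI and SF-12, the plan relies on missing-at-random given T1 and baseline terms alone and leaves informative T2 and T3 data unused. The bias in the PDI contrast is roughly 0 to 2.8 points, against a standard error of about 2.1 and a minimal important change of 13. The upper end needs opposite dropout patterns in the two groups, which nothing in the article suggests; one-group or unequal-rate patterns give 0.2 to 1.4.

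Only the 184, the 30% (20% in the cohort) and the 13 points come from the article. The SD, correlations and dropout relations are assumptions, and bias scales with the SD. The standard error takes 184 as enrolled; if 184 were the number with T4 data, it would be 12.1 × √(2/92) = 1.8. SF-12 shares the structure, but no size was calculated for it. The proposal is a worthwhile, inexpensive improvement, not the correction of an invalid analysis.

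**What to change.** Keep the planned mixed model. Limit the stated reason for not imputing to outcomes measured on all four occasions, and add one pre-specified analysis of T4 PDI and SF-12:

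- Use multiple imputation, or a joint likelihood model, with the available T2 and T3 NRS and EQ-5D-5L values as auxiliaries, together with the T1 values.
- Put every term of the analysis model into the imputation model: group, network, months in NPRL2.0 and the T1 covariates. Leaving out months of participation could weaken the learning-curve estimate.
- Report dropout by group and by last observed interim status, so that readers can judge which row of the table applies.

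No new data are needed, and multiple imputation is already planned for other variables. The cost is some wording and programming, plus an imputation model that must be specified and fitted with about 64 completers per group. It reduces rather than removes the bias where NRS and EQ-5D-5L are imperfect proxies for disability or were themselves not returned, and it adds nothing for patients who leave straight after T1.
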